|                                                                 | 
Each participant will remain at the study site for at least one hour (+30 minutes) to be observed for any immediate reactogenicity complaints associated with the Day 1 treatment.
 

Group	N	Day 1 Observer blind IP or Placebo administered	

MIMIX MAP Dose	

1	15	15 µg	

2	15	7.5 µg	

3	15	Placebo	

 
Participants will be followed for up to 180 days post immunization and evaluated during clinic visits on Study Days 2 (+1), 4 (+1), 8 (±2), 15 (±2), 29 (±2), 57 (±2), 85 (±7), 119 (±7), (final end of study visit) 180 (±7) following vaccination.
 
Participants will be contacted telephonically when an in-person visit is not scheduled through 8 days after treatment and will be assessed for solicited systemic and local adverse reactions and adverse events (AE) through Study Day 8, and solicited erythema and pigmented coloration on Study Days 15, 29, 57 and 180. Unsolicited AEs will be assessed from Study Days 1 through Day 29 after vaccination. Photographs of the treatment sites will be taken at each study visit through Day 57 and then at the end of study visit (Day 180).
                                                                                                                                                                                                                                                                                                                                                                                                                                                                                                                                                                                                                                                                                                                                                                                                                                 | Group          | N | Day 1 Observer blind IP or Placebo administered | MIMIX MAP Dose | 1 | 15 | 15 µg | 2 | 15 | 7.5 µg | 3 | 15 | Placebo |

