| STUDY SCHEDULE     | 
There will be a Screening window that is up to 30 days where all necessary assessments will be conducted to determine eligibility prior to randomization on study Day 1. Investigational product (test article) administration will occur on Day 1 for each randomized subject and will be given by an unblinded administrator.
 
In-clinic safety evaluations will be performed at screening, at Day 1 before and after administration of the test articles, and at Days 2 (+1), 4 (<math>\pm 1</math>), 8 (<math>\pm 2</math>), 15 (<math>\pm 2</math>), 29 (<math>\pm 2</math>), 57 (<math>\pm 2</math>), 85 (<math>\pm 7</math>), 119 (<math>\pm 7</math>) and 180 (<math>\pm 7</math>).
 
Telephone calls from the site to the participant will be made on Days 5, 6 and 7.
 
Photographs of the MIMIX MAP application site will be taken on the day of administration (pre-dose, then 1 (<math>\pm 2</math>), 30 (<math>\pm 5</math>) and 60 (<math>\pm 5</math>) minutes post-MAP removal), and on Days 2 (+1), 4 (<math>\pm 1</math>), 8 (<math>\pm 2</math>), 15 (<math>\pm 2</math>), 29 (<math>\pm 2</math>), 57 (<math>\pm 2</math>) and 180 (<math>\pm 7</math>).
 
Specimens for assessment of immune response will be collected at screening, before first vaccination on Day 1, and on Days 29 (<math>\pm 2</math>), 57 (<math>\pm 2</math>), 85 (<math>\pm 7</math>), 119 (<math>\pm 7</math>) and 180 (<math>\pm 7</math>).
 
A detailed schedule of assessments appears in Table 5.
                                                                                                                                                                                                                                                                              |

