| SAFETY ASSESSMENTS | 
On day of vaccination, observe study participants in clinic for a minimum of 1 hour (+ 30 minutes) post-dose as directed by the study physician or designate.
 
Solicitation of local and systemic reactogenicity events will be captured via clinic visits as applicable using standardized grading. Reactogenicity assessment will also include unsolicited complaints.
 
All local and systemic reactogenicity reporting in the 7 days after immunization will be supported via in-person visits and telephonically. Calls are to query for any adverse events using, complete Appendix 1, 2 and the systemic section of Appendix 3, and to determine if an on-site visit is needed.
 
Skin tolerability assessments including pain, induration, tenderness, erythema and edema (Appendix 1: Local Tolerability Scoring) will be carried out on the day of administration (pre-dose, then 1 (<math>\pm 2</math>), 30 (<math>\pm 5</math>) and 60 (<math>\pm 5</math>) minutes post-MAP removal), and on Days 2 (+1), 4 (+1), 8 (<math>\pm 2</math>). Erythema assessments only will be carried out on Days 15 (<math>\pm 2</math>), 29 (<math>\pm 2</math>), 57 (<math>\pm 2</math>) and 180 (<math>\pm 7</math>).
 
Other local tolerability assessments of the MAP application site including bruising, itching, skin flaking and pigmented skin coloration (Appendix 2: Other Local Tolerability Scoring) will be carried out on the day of administration (pre-dose and 60 (<math>\pm 5</math>) minutes post-MAP removal), and on Days 2 (+1), 4 (<math>\pm 1</math>), 8 (<math>\pm 2</math>). Pigmented coloration assessments only will be carried out on Days 15 (<math>\pm 2</math>), 29 (<math>\pm 2</math>), 57 (<math>\pm 7</math>) and 180 (<math>\pm 7</math>).
 |

|                                   |                                                                                                                                                                                                                                                                                                                                                                                                                                           |                               |

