On Day 2 (24 hr post treatment), participants will return to the clinic for an abbreviated physical exam, vital sign measurements, a review of any systemic or local site reactions (skin tolerability and other local tolerability assessments) and for further application site photographs to be taken.

On Day 4 (3 days post treatment), participants will return to the clinic for an abbreviated physical exam, vital sign measurements, a review of any systemic or local site reactions (skin tolerability and other local tolerability assessments) and for further application site photographs to be taken. Blood samples will be collected for hematology and chemistry.

On Day 5, 6 and 7 a phone call will be made to participants to ask about spontaneous adverse events or changes on concurrent medication.

On Day 8 ( $\pm 1$  day) participants will return to the clinic for an abbreviated physical exam, vital sign measurements, a review of any systemic or local site reactions (skin tolerability and other local tolerability assessments) and for further application site photographs to be taken.

On Day 15 (+/- 2 day), participants will return to the clinic for an abbreviated physical exam, vital sign measurements, for erythema ([Appendix 1: Local Tolerability Scoring](#)) only and pigmented coloration assessments ([Appendix 2: Other Local Tolerability Scoring](#)) only and for further application site photographs to be taken.

On Day 29 (+/- 2 day) participants will return to the clinic for an abbreviated physical exam, vital sign measurements, for erythema ([Appendix 1: Local Tolerability Scoring](#)) only and pigmented coloration assessments ([Appendix 2: Other Local Tolerability Scoring](#)) only and for further application site photographs to be taken. Blood samples will be collected for hematology, biochemistry and immunogenicity analysis.

On Day 57 (+/- 4 days), participants will return to the clinic for additional application site photographs, an abbreviated physical exam, vital sign measurements and for erythema ([Appendix 1: Local Tolerability Scoring](#)) only and pigmented coloration assessments ([Appendix 2: Other Local Tolerability Scoring](#)) only. Blood samples will be collected for immunogenicity analysis.

On Day 85 (+/- 7 days), participants will return to the clinic for an abbreviated physical exam and vital sign measurements. Blood samples will be collected for immunogenicity analysis.

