- l. All photographs should be taken with the study specific iPhone or the study specific DermLite DL4 Dermatoscope attached to the iPhone. Subject ID, Subject initials, and timepoint should be included in each iPhone photograph with a label. On Study Day 1, iPhone photographs should be taken of the treatment site both pre dosing (within 30 minutes prior to dosing) and 1 + 2 minutes, 30 ± 5 and 60 ± 5 minutes post removal of the MAP. iPhone photographs will also be taken a single time on Days 2, 4, 8, 15, 29, 57 and 180. For each iPhone photograph hold the phone 8-10 cm above the Application site, take one, in focus, 1x magnification photo. Capture the Application site and label.
- Dermatoscope images will be taken with the Dermatoscope attached to the iPhone, the lens spacer rotated to '0' and the faceplate removed. The image will be taken with the lens spacer gently touching the application site periphery. The rim of the Dermatoscope lens spacer should be wiped with alcohol before and after use. Photographs with the Dermatoscope attached to the iPhone should be taken of the treatment site pre dosing (within 30 minutes prior to dosing) and a single time on Days 29 and 180. Photographs with the Dermatoscope should be 'captioned' using the iPhone 'add a caption' function. The Caption should include the Subject ID, initials and timepoint. All photos should be taken under consistent lighting conditions. All photographs will be uploaded to a secure file system, BOX. Please see VX-103-01 Imaging Instructions for additional instructions.
- m. Standard adverse event collection will take place from the time the informed consent is signed through Day 29. This will capture all adverse events that are not included from the solicited adverse event collection appendices.
- n. These calls are to query for any adverse events, complete Appendix 1, 2 and the systemic section of Appendix 3 and determine if an on-site visit is needed.

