### **Itching**

Participants will be asked the degree of itching they are experiencing on average in the last 24 hours:

Grade Description:

- 0 NONE
- 1 MILD
- 2 MODERATE
- 3 SEVERE

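### Day 3 has no scheduled contact although the synopsis promises a call on every day without a visit, and Section 3 describes the Day 5–7 calls differently from the synopsis and Table 5

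*Protocol*

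**What the plan says.** **Which days have a contact.** The study-design row of the protocol synopsis says: "Participants will be contacted telephonically when an in-person visit is not scheduled through 8 days after treatment". The same sentence adds that participants "will be assessed for solicited systemic and local adverse reactions and adverse events (AE) through Study Day 8". The study-schedule row gives the actual days: "In-clinic safety evaluations will be performed at screening, at Day 1 before and after administration of the test articles, and at Days 2 (+1), 4", continuing with Day 8 and the later visits. It then adds: "Telephone calls from the site to the participant will be made on Days 5, 6 and 7". Section 3 lists the same visits and the same three calls.

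**What the calls collect.** Section 3 says: "On Day 5, 6 and 7 a phone call will be made to participants to ask about spontaneous adverse events or changes on concurrent medication". The safety-assessments row of the synopsis says: "Calls are to query for any adverse events using, complete Appendix 1, 2 and the systemic section of Appendix 3". Footnote n of Table 5 agrees with the synopsis: "These calls are to query for any adverse events, complete Appendix 1, 2 and the systemic section of Appendix 3".

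**Why these data count.** Section 12.4.1 includes local and systemic reactogenicity events among the primary endpoints. The itching item in Appendix 2 has a short recall period: "Participants will be asked the degree of itching they are experiencing on average in the last 24 hours".

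**The concern.** The general commitment and the list of days cannot both be followed. A site working from the list makes no contact on Day 3. A site working from the study-design row would have to make a call that the schedule does not contain. The protocol describes no participant diary that would cover the missing day.

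Day 3 falls early in the solicited period. An item with 24-hour recall, asked on Day 4, reaches back only to about Day 3, so the stretch from Day 2 to Day 3 is not recovered for itching. More generally, a reaction that comes and goes between contacts is known only from what the participant remembers, and was never graded while it was present.

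The second conflict concerns content. Up to three sites take part. If one reads Section 3 and another reads footnote n, they collect different things on Days 5, 6 and 7 for the same endpoint, and missed solicited readings cannot be recovered later.

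**Working it through.** There is no stated figure to reproduce, so the check is a count of contact days and a comparison of the texts.

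**1. Nominal coverage of Study Days 1–8** (synopsis study-schedule row; Section 3)

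| Study Day | 1 | 2 | 3 | 4 | 5 | 6 | 7 | 8 |
|---|---|---|---|---|---|---|---|---|
| Visit | yes | yes | – | yes | – | – | – | yes |
| Call | – | – | – | – | yes | yes | yes | – |

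Four visits plus three calls make 7 days with a contact, and 8 − 7 = 1 day (Day 3) has none. Coverage is 7/8 = 87.5%. For 45 participants that is 45 × 1 = 45 uncovered participant-days out of 45 × 8 = 360.

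**2. Do the visit windows close the gap?** The Day 2 visit may fall on Day 2 or 3. The Day 4 visit may fall on Day 4 or 5 under the +1 window, or on Day 3, 4 or 5 under ±1. The earliest Day 8 visit is Day 6 under the synopsis window of ±2. Days 2, 3 and 4 can therefore be served by at most two visits, so at least one of the three stays empty. Over all combinations, with the calls counted as solicited contacts, 1 to 3 of the eight days are uncovered, whichever Day 4 window is used. An example with three is visits on Days 3, 5 and 9, which leave Days 2, 4 and 8 empty. Section 3 gives ±1 for Day 8, and this does not change the range.

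**3. Longest early gap.** At nominal timing, Day 2 to Day 4 is 4 − 2 = 2 days, about 48 hours. If the Day 4 visit is held on Day 5, the interval is 5 − 2 = 3 days, about 72 hours, with no contact on Day 3 or Day 4.

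**4. What the calls collect**

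| Source | Content of the Day 5–7 calls |
|---|---|
| Section 3 | Spontaneous adverse events, medication changes |
| Synopsis, study-design row | Telephone contact and solicited assessment through Day 8, in one sentence |
| Synopsis, safety-assessments row | Appendices 1 and 2, systemic part of Appendix 3 |
| Table 5, footnote n | Appendices 1 and 2, systemic part of Appendix 3 |
| Table 5, rows | Appendix 1, 2 and 3 rows ticked in the telephone column |

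The last line comes from counting cells. Each readable row has 17 cells, the only telephone tick is in cell 8, and all three Appendix rows are ticked there. The table's header is not legible in the text at hand, so the days belonging to the columns are inferred from the pattern of ticks. On that reading there is no separate Day 3 column.

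Under the synopsis and Table 5, solicited coverage is 7 of 8 days. Under a literal reading of Section 3 it would be Days 1, 2, 4 and 8 only, or 4 of 8.

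**5. Day 4 window.** It is +1 in the study-design row and ±1 in the study-schedule row. The safety-assessments row uses +1 for the Appendix 1 scores and for the clinic visits, and ±1 for the Appendix 2 scores. Section 3 states no window for this visit.

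**The case against.** The best defence is that the study-design row is a general sentence, while the study-schedule row names the days and should govern. The omission is then one day out of eight. Day 1 already has three timed skin assessments after patch removal, Days 2 and 4 are clinic visits, and participants are told to contact the clinic with any concern. The primary objective is descriptive and the schedule is the same in every arm, so no bias between arms is shown. Erythema and induration are graded by measured diameter, which a call captures less well than a visit. All of this stands and limits the size of the point. It does not remove the contradiction, because both rows are current text and the protocol does not say which prevails.

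Two stronger readings are tempting and are not supported.

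- A reader might infer from Section 3 that the calls are for unsolicited events only and that half of the solicited days are lost for all 45 participants. Section 3 does not say only, and the synopsis, footnote n and the Table 5 ticks all put the solicited scales on the calls. Section 3 also defers to Table 5, although that sentence is worded for visits. The 4-of-8 figure describes a site that ignores those texts, not the plan.
- A reader might infer that the halting rules for grade 3 reactions lasting 48 hours or more cannot be applied. Section 10.1.1 requires start and end dates for every adverse event, so duration is recorded. At nominal timing, a reaction lasting 48 hours or more would also reach the Day 2 or the Day 4 contact. When the Day 4 visit is held on Day 5, such a reaction could begin and end between contacts. Its grade and dates would then rest on recall, which is a weaker record but still a record.

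**Conclusion.** The point holds in a limited form. Day 3 has no scheduled contact, contrary to the study-design row of the synopsis. Planned solicited coverage of a primary endpoint is therefore 7 of 8 days, and the early gap between solicited contacts can reach about 72 hours when the Day 4 visit runs a day late. The Section 3 description of the Day 5–7 calls is a separate wording conflict. It costs data only if a site follows it literally.

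The Day 3 finding rests on legible text in the synopsis and Section 3 and does not depend on the Table 5 header. The count takes the nominal days as planned and treats the calls as solicited contacts, as the synopsis and footnote n say. No estimate is offered of how many reactions would be missed, because the protocol gives no figure from which to derive one. The matter is worth correcting before dosing, but it does not undermine the primary analysis.

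**What to change.** 1. Add a Day 3 solicited call to the study-schedule row of the synopsis, to Section 3 and to Table 5, so that the schedule matches the study-design row. Nominal solicited coverage then becomes 8 of 8 days.
2. Reword the Section 3 sentence so that the calls complete Appendix 1, Appendix 2 and the systemic section of Appendix 3, as footnote n says, in addition to asking about other adverse events and medication.
3. Reconcile the Day 4 window so that one value appears throughout.

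The cost is one extra call for each of 45 participants, about 45 short calls in all, plus a few amended lines. The calls are already promised by the study-design row. The limitation is that diameters reported by telephone will be less reliable than those measured in clinic, so the Day 3 call will add more on symptoms than on measured reactions.

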
## 1. INTRODUCTION

### 1.1 Background

Although influenza vaccines reduce the risk of flu illness by between 40% and 60% among the overall population, factors such as age and the degree of antigenic match are known to affect their effectiveness ([Allen & Ross, 2018](#); [Belongia et al., 2016](#); [Darvishian et al., 2014](#); [Rondy et al., 2017](#)).

A recently emerging factor affecting influenza vaccine effectiveness is waning immunity within the influenza season. Although, several studies have reported decreases in vaccine effectiveness over the influenza season, waning effects have not been observed consistently across age groups, virus subtypes, and seasons. Still, the emerging data has prompted the Center for Disease Control (CDC) to provide a timing recommendation for receipt of the influenza vaccine along with the suggestion that getting vaccinated early (in July or August) is likely to be associated with reduced protection later in the flu season ([CDC, 2020](#)). A recent study has suggested that the waning immunity may be linked to the rapid decline of bone marrow plasma cells (which correlate with circulating levels of antibody secreting cells) that are responsible for the long-term maintenance of serum antibody levels ([Davis et al., 2020](#)).

There has been a long-standing interest in intradermal influenza vaccines because of their dose-sparing potential and therefore their ability to mitigate potential vaccine shortages, which could occur from unanticipated loss of expected supplies or from excessive demand owing to high rates of infection, such as during pandemics ([Kenney et al., 2004](#); [La Montagne & Fauci, 2004](#)). A recent meta-analysis conducted ([Egunsola et al., 2021](#)) reported no statistically significant difference in seroconversion rates between the 3- $\mu$ g, 6- $\mu$ g, 7.5- $\mu$ g, and 9- $\mu$ g intradermal vaccine doses and the 15- $\mu$ g intramuscular vaccine dose for each of the H1N1, H3N2, and B strains, but rates were significantly higher with the 15- $\mu$ g intradermal dose compared with the 15- $\mu$ g intramuscular dose for the H1N1 strain (rate ratio [RR], 1.10; 95% CI, 1.01-1.20) and B strain (RR, 1.40; 95% CI, 1.13-1.73). Thus, intradermal delivery has the potential not only for dose sparing but also to improve immune responses to influenza vaccines.

In summary, while current influenza vaccines are safe and offer moderate protection against influenza associated disease, unmet needs remain. There is a current need for vaccine platforms that can improve vaccine effectiveness, extend the durability of the immune response while also providing dose sparing capabilities.

### 1.2 Vaccine Design

The MIMIX MAP is a novel intradermal MAP vaccination system comprising microneedles of silk fibroin and vaccine antigen designed for prolonged release of antigen into the skin, the largest immune organ in the body. Sustained antigen presentation is known to modulate the magnitude, duration and specificity of immune responses. In mouse models of MIMIX

vaccination we have observed sustained stimulation of germinal center responses, trends towards an improvement in the magnitude of HAI titers particularly at timepoints more than 1 month post dosing, a broadening in immunity against drifted influenza strains, and stronger antigen-specific T cell responses than observed with bolus intramuscular (IM) delivery (Stinson et al., 2021). These attributes have the potential to address some of the shortcomings of current licensed influenza vaccines.

The MIMIX MAP includes the Microneedle Array and a Backing that comprises an Adhesive, and a structural Plastic Film as shown in Figure 1. The Microneedle Array is made of up of a regular pattern of microneedles that include the antigen containing Tip (DP) and a structural base. Each MIMIX MAP is produced by an additive manufacturing approach using a silicon mold that defines the microneedle shape. The MAP is separated from the silicon mold through assembly to the Backing.

**Figure 1: The MIMIX MAP**

[figure not shown]

After separation from the silicon mold the MAP is packaged in a Carrier with a Retainer to form the MAP Cartridge; a single-use, disposable subsystem that consists of the MAP, a Carrier, and Retainer (Figure 2). The Carrier is designed to hold the MAP and mediates mounting to a spring-loaded Applicator. The Retainer secures the MAP in the Carrier. The MAP Cartridge is encased in a polystyrene Tray and inserted in a foil lined pouch with a desiccant for shipping and storage at 4°C. The MAP Cartridge is the only part of VX-103 that contacts the participant.

